#### Plans to promote participant retention and complete follow-up {18b}

All attempts will be made to encourage patients to adhere to the study follow-up schedule. Contact information for the patient and two close contacts are obtained to maximize our chances of maintaining contact. Each patient will be reminded by phone the week preceding their follow-up appointment. To ease the burden of follow-up, all study patients will also be seen for follow-up in a dedicated study clinic and will have the fees for their radiographs, follow-up, and necessary bloodwork covered by the study. In the event a patient is unable to make a follow-up appointment in their dedicated follow-up window, a telephone fracture-related infection screen will be completed and attempts to reschedule future appointments will be made.

Patients are made aware during the consenting process that enrollment in the study that patients will incur the standard fees for evaluation and treatment; however, to decrease the financial burden of study participation and follow-up, the following procedures will be covered for all participants:Systemic antibiotics for all screened patientsPreoperative, postoperative, and 2-week creatine levelsC-reactive protein levels at all study follow-upsAll follow-up radiographsFollow-up consolation fees for the follow-up clinical evaluations at a dedicated study clinic to minimize wait timesTwo intraoperative cultures for any study patient who undergoes a reoperation

### Data management {19}

Three trained research coordinators will be responsible for all data collection, working in conjunction with providers at the study site when required. All data will be entered and stored on REDCap, a secure data management platform only accessible to members of the study, using portable laptops and phones. The REDCap system uses a variety of mechanisms to ensure data quality including skip logic, range checks, and data type checks. A member of the coordinating center will do weekly checks on the entered data for the duration of the study to ensure completeness. The full range of data quality and monitoring can be found in the trial DSMP.

### Confidentiality {27}

All data will be maintained on REDCap, a secure data management tool that requires dual authentication and is only accessible to those approved to work with study data. In addition, all participants are assigned a unique identifier. This identifier is used for all data monitoring and analysis. Patient identifying information is only available to the local study coordinators and one member of the coordinating center.

### Plans for collection, laboratory evaluation, and storage of biological specimens for genetic or molecular analysis in this trial/future use {33}

The standard laboratory protocols will be used at MOI for the collection and testing of blood specimens for all study-related tests including serum creatinine and C-reactive protein. Should a study participant undergo reoperation, cultures will be collected and performed at the Muhimbili University of Health and Allied Sciences (MUHAS) laboratory. No biological specimens will be stored for genetic or molecular analysis in the future.

## Statistical methods

### Statistical methods for primary and secondary outcomes {20a}

#### Statistical methods for primary outcome

The primary analysis will surround the occurrence of FRI as a binary outcome. This will be done through a binomial regression with the complementary log–log link, allowing for the available person-time to be used. The estimated effect will be the relative hazard. The analysis will be two-sided, with a type I error rate (alpha) of 0.05. Each trial is separate, with an independent alpha.

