### Outcomes {12}

#### Primary outcomes

The primary outcome of this study will be the occurrence of fracture-related infection (FRI), a binary outcome. FRI is a consensus definition of infection after fracture treatment that is clinically diagnosed by an orthopedic surgeon based on any of the following four diagnostic criteria: (1) fistula, sinus, or wound breakdown; (2) purulent drainage from the wound or presence of pus during surgery; (3) phenotypically indistinguishable pathogens identified by culture from at least two separate deep tissue/implant specimens; or (4) presence of microorganisms in deep tissue taken during an operative intervention, as seen on histopathological examination. It is expected that the peak diagnosis time will occur between 6 weeks and 6 months; however, these criteria will be assessed by an orthopedic surgeon at every follow-up time point.

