**Fig. 2 Fig2:**
[figure not shown]
Study flow diagram

**Table 1 Tab1:** GO-Tibia schedule of events

Assessment	Hospital				Outpatient					
	Pre-surgery		Surgery	Post- surgery, ≤ 48 h postop	2 weeks	6 weeks	3 months	6 months	9 months	12 months
	Screen	Enroll								
Radiographs	●			●			●	●	●	●
Informed consent		●								
Serum creatinine		●		●						
Randomization			●							
Intervention			●							
Baseline data				●						
Contact information				●						
EQ-5D				●			●	●	●	●
Outcomes										
Assessment					●	●	●	●	●	●
FIX-IT							●	●	●	●
WPAI						●	●	●	●	●
C-reactive protein					●	●	●	●	●	●
Adverse event										
Screen					●	●	●	●	●	●

Post-discharge follow-up assessments are performed at 2 weeks, 6 weeks, 3 months, 6 months, 9 months, and 12 months after the intervention.

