### Sample size {14}

Data from a prior randomized control trial conducted at Open Tibia Trial (MOI) and the FLOW trial was used to estimate the base rate of reoperation at 12% [13, 14]. Previous literature suggests using local aminoglycoside antibiotics provides a relative risk reduction of approximately 50% for FRI [15]. An absolute risk reduction of 12 to 6% with a two-tailed alpha of 0.05, a power of 80%, and an estimated loss to follow-up rate of 20% suggests a sample size of 445 individuals per treatment arm for a total of 890 enrolled patients.

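### On its most natural reading the primary cloglog model assumes a constant infection hazard, which does not fit the expected peak; the hazard ratio then shifts if loss to follow-up differs between arms

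*Protocol article*

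**What the plan says.** Under {20a}, Statistical methods for primary outcome, the protocol article states: "The primary analysis will surround the occurrence of FRI as a binary outcome". The model is specified in one sentence, "This will be done through a binomial regression with the complementary log–log link, allowing for the available person-time to be used", and the effect measure in the next, "The estimated effect will be the relative hazard". No interval, repeated record, offset or time effect is mentioned.

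Three other places bear on this:

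- {12}, Primary outcomes, on timing: "It is expected that the peak diagnosis time will occur between 6 weeks and 6 months".
- {13}, Participant timeline, on when FRI can be observed: "Post-discharge follow-up assessments are performed at 2 weeks, 6 weeks, 3 months, 6 months, 9 months, and 12 months after the intervention".
- {14}, Sample size, on attrition: "an estimated loss to follow-up rate of 20" per cent. No split by arm or by time is given.

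Under {20c}, missing outcomes are not imputed. The exploratory regression of missingness and observation time lists gender, injury severity, travel cost and age, but not treatment arm.

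**The concern.** A binomial cloglog model with one binary record per patient and offset log(t) sets the probability of an event by time t at 1 − exp(−λt). Each month of follow-up then carries the same risk. If infections cluster before 6 months, follow-up lost later removes much person-time and little risk. The model credits the arm with more late loss with too little exposure, so that arm's rate looks too high.

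The distortion cancels when both arms lose follow-up alike. When they do not, it passes into the primary hazard ratio, its type I error and its power. None of the supporting analyses in the article checks the time assumption. The Fisher test is on reoperation, and the sensitivity analyses vary baseline covariates. Loss by arm becomes known only as follow-up accrues, when a change of model would look data-driven.

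**Working it through.** **Inputs from the protocol article.** Risks of 12% and 6%, two-sided alpha 0.05, power 80%, loss 20%, 445 per arm ({14}); visits at 2 and 6 weeks and 3, 6, 9 and 12 months ({13}); peak between 6 weeks and 6 months ({12}).

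**Assumptions, not in the documents.** The share of cumulative hazard in 0–6 weeks / 6 weeks–6 months / 6–12 months is 20/70/10% in the main case, with 25/60/15% and 10/60/30% as variants. Loss by arm and its timing are also assumed. Loss is independent of infection risk. Person-time is follow-up to the last attended visit.

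**Step 1. The plan's own figure.** With pooled variance and no continuity correction:

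n = [1.96·√(2·0.09·0.91) + 0.8416·√(0.12·0.88 + 0.06·0.94)]² / 0.06² = (0.793 + 0.339)² / 0.0036 ≈ 356

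356 / 0.8 = 445 per arm, which matches "a sample size of 445 individuals per treatment arm for a total of 890 enrolled patients". The implied hazard ratio is ln(0.94)/ln(0.88) = 0.484.

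**Step 2. Hand check under the null (true HR 1).** Take the 20/70/10% shape with loss after the 6-month visit. Each lost patient gives up 6 of 12 months but only 10% of the cumulative hazard.

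| Loss control/gentamicin | Mean months, control | Mean months, gentamicin | Hazard retained, control | Hazard retained, gentamicin | Rate ratio |
|---|---|---|---|---|---|
| 20/20% | 10.8 | 10.8 | 0.98 | 0.98 | 1.00 |
| 15/25% | 11.1 | 10.5 | 0.985 | 0.975 | (0.975/10.5)/(0.985/11.1) = 1.046 |
| 10/30% | 11.4 | 10.2 | 0.99 | 0.97 | (0.97/10.2)/(0.99/11.4) = 1.095 |

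The large-sample limits of the fitted one-record model are 1.000, 1.047 and 1.096. With true HR 0.484 they are 0.484, 0.506 and 0.530.

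**Step 3. Range.** Across the three shapes and six loss timings, a 10-point imbalance in either direction moves the null HR to between 0.955 and 1.047. A 20-point imbalance moves it to between 0.913 and 1.096. Loss after the 6-month visit is the worst timing; loss after the 2-week visit gives about 0–1.5%. More loss on gentamicin usually raises the HR, and more loss on control usually lowers it. The sign turns slightly for early loss when few infections occur in the first 6 weeks. With a constant hazard there is no shift under any loss pattern.

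**Step 4. Simulation** (445 per arm, 1,500 trials per case, 20/70/10% shape, loss after the 6-month visit), comparing the one-record model with a cloglog model that has one intercept per visit interval:

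| Loss | Null HR, one record | Null HR, intervals | Type I error, one record | Type I error, intervals | Power, one record | Power, intervals |
|---|---|---|---|---|---|---|
| 20/20% | 1.000 | 1.000 | 4.9% | 5.1% | 89.3% | 89.3% |
| 15/25% | 1.053 | 1.006 | 5.5% | 4.5% | 84.0% | 88.9% |
| 10/30% | 1.098 | 1.003 | 6.8% | 4.5% | 77.7% | 87.9% |

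The standard error of the log HR is essentially the same in both models: about 0.20 under the null and 0.24 under the alternative.

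**Step 5. Cross-check of type I error at 10/30%.** The shift is ln(1.096) = 0.092, and 0.092/0.197 = 0.465 standard errors. P(Z > 1.96 − 0.465) + P(Z < −1.96 − 0.465) = 0.067 + 0.008 = 7.5%. The simulated 6.8% has a Monte Carlo error of √(0.068·0.932/1500) = 0.65 points, so about 7–8% is a fair statement. At 15/25% the same arithmetic (0.046/0.197 = 0.23) gives 5.6%.

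**The case against.** **The model form is inferred.** A reader might infer that the protocol prescribes a constant hazard. It does not: it never mentions a single record, an offset or a constant hazard. The sentence also fits a model with visit-interval intercepts, or one with log time as a covariate, and neither assumes a constant hazard. The full protocol or SAP may settle this. That stands, and the point is conditional on the reading. The text still leans towards one record per patient. It speaks of a binary outcome, and {20a} and {20c} treat observation time as one quantity per patient, contrasting the primary model with a 2 × 2 table that ignores it.

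**Unequal loss has no stated basis.** A reader might also infer that the planned hazard ratio is biased as it stands. The documents do not support that either. They give 20% loss overall, a single intraoperative injection, masked participants and assessors, and the same retention measures for everyone. With equal loss the null HR is unbiased. A 10/30% split is a stress case. At 15/25% the shift is about a quarter of a standard error, and a simulated type I error of 5.5% cannot be told from 5% with 1,500 runs. This also stands.

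**The interval model is not wholly free.** Before loss, about 445 × 0.12 + 445 × 0.06 = 80 events are expected. Under the 20/70/10% shape each of the last two intervals holds about 5% of them, or 4 events, so an empty interval is possible. Missed visits are replaced by a telephone screen ({18b}), so the interval of onset may be uncertain. Both need a rule, but neither is a reason to prefer the constant-hazard form.

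**No imputation is beside the point.** The interval model does not impute either.

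**Conclusion.** The concern holds in conditional form. On the most natural reading, the primary model assumes a constant hazard that does not fit the timing the protocol itself expects. The consequence depends on the arms losing follow-up differently:

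- equal loss: no null bias;
- 15/25%: null HR shifted by up to about 5%, type I error close to nominal, power 84% against 89%;
- 10/30%: null HR shifted by up to about 10%, type I error about 7–8%, power about 78% against 88%.

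The last two lines are for the worst timing (loss after the 6-month visit); other timings give less. They rest on assumed hazard shapes and loss splits, and on loss unrelated to infection risk. This is a weakness worth removing in advance, because a standard alternative matched its power when loss was equal and kept its error rate when loss was not. It is not evidence that the trial's hazard ratio will be wrong.

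**What to change.** State in the primary analysis that the binomial cloglog model uses one record per patient per visit interval (0–2 weeks, 2–6 weeks, 6 weeks–3 months, 3–6, 6–9 and 9–12 months), up to FRI or the last assessment, with interval as a factor. The treatment coefficient remains the log relative hazard. Add two rules: merge adjacent intervals if one has no events in the two arms combined, and say how the interval of onset is assigned when a visit was missed. Keep the single-record person-time version at most as a sensitivity analysis.

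The cost is a few sentences, up to five extra nuisance parameters and the onset rule. Data, software and estimand do not change, and the simulated standard errors did not increase. The change does not deal with loss related to infection risk, which neither model solves.

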### Statistical methods used for secondary and additional outcomes

These analyses are designed to provide additional insight and support for the primary analysis and to assess whether the methodological choices we made had an undue effect on the results. In reporting, they will be sharply distinguished from the primary outcome. Additional sensitivity analyses will be conducted based on the following variables as baseline covariates: Gustilo-Anderson fracture type, OTA Open Fracture Classification for contamination, time from injury to first debridement, and method of fixation. We will make available the results of Fisher’s exact test on the 2 × 2 cross-tabulation of the reoperation binary outcome and the treatment assignment. This does not consider the observation time and thus is an independent statistical procedure and may yield different decisions than the primary prespecified analysis. We will also report the 95% confidence interval for the risk difference between the groups. Because this will be conducted by an independent regression (binomial regression with the identity link), these new findings may be statistically inconsistent with the main analysis. Thus, we will only report 95% confidence intervals, omitting *P*-values.

The risk difference is interpretively important and may be useful in future meta-analytic studies. Intent-to-treat analysis is recommended but impossible when the primary outcome is missing. We will conduct exploratory regression of missingness and observation time, using the following predictors when appropriate: gender, severity of injury, cost of travel to clinic, and age.

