### Trial design {8}

This is a randomized, masked, placebo-controlled superiority trial to evaluate the efficacy of locally administered gentamicin versus placebo in the prevention of fracture-related infection in open tibia fracture patients. Patients will be randomized using randomly permuted blocks in a 1:1 allocation ratio.

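### Gustilo-Anderson class and OTA contamination enter only sensitivity analyses of FRI; placing them in the primary model would be a cheap, modest gain in efficiency

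*Protocol article*

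**What the plan says.** The section on statistical methods for the primary outcome specifies a binomial regression of FRI with a complementary log-log link, "allowing for the available person-time to be used", with the relative hazard as the effect measure. It adds: "The analysis will be two-sided, with a type I error rate (alpha) of 0.05". No covariate is named.

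The next section, on secondary and additional outcomes, brings covariates in: "Additional sensitivity analyses will be conducted based on the following variables as baseline covariates: Gustilo-Anderson fracture type, OTA Open Fracture Classification for contamination". Two further covariates are listed there: the fixation method, and how long after injury the first debridement took place. The section says these analyses will be kept clearly apart from the primary result. The section on additional analyses {20b} uses nearly the same factors as subgroups and classes conclusions drawn from subgroups or adjustments as hypothesis-generating, not to be highlighted.

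On allocation, Trial design {8} says: "Patients will be randomized using randomly permuted blocks in a 1:1 allocation ratio". Neither that section nor Sequence generation {16a} names a stratification factor. Under Intervention description {11a}, randomisation follows debridement, stabilisation and the surgeon's confirmation that the wound can be closed primarily.

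**The concern.** Two factors that the sponsor already intends to collect and model are kept out of the primary estimate. Both describe the wound as it stands before allocation, so they are legitimate baseline covariates. Adjusting a hazard-type model for baseline factors that predict the outcome usually raises power at a fixed sample size. It also takes chance imbalance in those factors out of the treatment estimate.

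As written, if one arm happened to receive more class IIIA or heavily contaminated wounds, an adjusted estimate would be available, but the plan would give it only hypothesis-generating standing. What is at stake is some precision in the primary result and the standing of the estimate that answers the imbalance question.

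**Working it through.** **1. Reproduce the sample size.** Inputs from Sample size {14}: "An absolute risk reduction of 12 to 6% with a two-tailed alpha of 0.05, a power of 80" per cent, with 20% loss to follow-up. The 12% base rate is described there as a reoperation rate; the halving is cited for FRI ("provides a relative risk reduction of approximately 50% for FRI").

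n per arm = [1.96·√(2·0.09·0.91) + 0.842·√(0.12·0.88 + 0.06·0.94)]² / 0.06² = (0.793 + 0.339)² / 0.0036 ≈ 356.

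Enrolled per arm = 356 / (1 − 0.20) = 445, total 890. This matches the article exactly. Power at 356 per arm is 80.0%. The calculation has no covariate term, so it agrees with an unadjusted analysis.

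**2. Events and effect.** Expected events: 356 × 0.12 + 356 × 0.06 = 42.7 + 21.4 ≈ 64. Implied hazard ratio: ln(0.94)/ln(0.88) = 0.484. A model with treatment, two class terms and two contamination terms has five coefficients: 64 / 5 ≈ 13 events per term.

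**3. Power with and without adjustment.** The article gives no prognostic strengths and no factor prevalences, so both are assumptions. Trials were simulated with 356 evaluable per arm and overall risks of 12% and 6%, and analysed with the complementary log-log model. The four-factor runs (2,000 trials each) adjust for all four covariates in the article's list. The two-factor runs (3,000 trials each) adjust for class and contamination only.

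| Assumed prognosis | Adjusted for | Unadjusted | Adjusted | Gain (points) |
|---|---|---|---|---|
| None | four factors | 79.8% | 80.0% | 0.2 |
| Weak (hazard ratios 1.2 to 1.5) | four factors | 79.5% | 79.8% | 0.3 |
| Moderate (1.4 to 2) | four factors | 81.5% | 82.4% | 0.9 |
| Moderate (class risks 6/11/20%; contamination hazard ratios 1/1.5/2.5) | two factors | 80.2% | 81.7% | 1.5 |
| Strong (class risks 4/9/24%; contamination 1/2/4) | two factors | 81.0% | 83.8% | 2.8 |
| Strong (1.5 to 4) | four factors | 78.2% | 82.2% | 4.0 |

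Monte Carlo error per figure is √(0.8·0.2/2000) = 0.9 point for the four-factor runs and √(0.8·0.2/3000) = 0.7 point for the two-factor runs. The gains in the first three rows cannot be told from zero with confidence. No scenario showed a loss of power.

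**4. Type I error.** Null runs were made for the four-factor model at no, weak and moderate prognosis. Rejection rates were 3.7% to 5.0% unadjusted and 4.1% to 5.1% adjusted. The strong null scenario was not completed.

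**5. Chance imbalance.** For a binary factor with prevalence p, the SD of the between-arm difference is √(2p(1−p)/356): 2.7 points at p = 0.15, 3.4 at 0.30 and 3.7 at 0.50. Put d = 1.96·SD and let the factor have hazard ratio h. The unadjusted hazard ratio is then multiplied by about [1 + (p + d/2)(h − 1)] / [1 + (p − d/2)(h − 1)].

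At p = 0.30, d = 0.067, and the multiplier is 1.030 for h = 1.5, 1.053 for h = 2 and 1.088 for h = 3. Over p = 0.15 to 0.50 and h = 1.5 to 3 it runs from 1.025 to 1.088, that is, about 3% to 9%.

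For scale, the standard error of the log hazard ratio is roughly √(1/42.7 + 1/21.4) = 0.265. The shifts are ln(1.025)/0.265 = 0.09 to ln(1.088)/0.265 = 0.32 standard errors.

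**6. Estimand.** In the strong four-factor scenario the average estimated hazard ratio was 0.478 unadjusted and 0.464 adjusted, so the conditional and marginal values differ only slightly at these event rates.

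**Limits.** The simulations ignore varying person-time. The prevalences used (for example 30% class IIIA) are assumed.

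**The case against.** The strongest case against is that nothing here is wrong. An unadjusted primary analysis with prespecified adjusted sensitivity analyses is a standard, valid design. It matches the sample-size calculation, and it already covers these very covariates. For weak or moderate factors the gain is about the size of simulation error. Eligibility also narrows the spread of severity, since classes IIIB and IIIC are excluded and every wound must be closable primarily, which makes the strong scenarios harder to presume. All of this stands, and it limits the point to an efficiency improvement.

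A reader might infer more than the article supports:

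- *The trial is underpowered without adjustment.* It is not. The planned 80% is reached with the unadjusted comparison; what is forgone is power above that.
- *Chance imbalance biases the primary test.* It does not. Alpha and the confidence interval already allow for it, imbalance can fall either way, and a shift at the 1.96-SD limit is by definition about a 1-in-20 event.
- *These are known strong predictors of FRI in this population.* The article gives no figure.
- *Randomisation is known to be unstratified.* The article names no strata, but it condenses a fuller protocol that is not shown.
- *The plan sets up two rival headline results.* The text says the opposite: it ranks the adjusted analyses below the primary one.

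The objection does not remove the case for change. Where the covariates go is a stated choice, not a detail left open, and the alternative costs almost nothing.

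**Conclusion.** The point holds as a low-cost improvement. The primary model as described leaves out two factors that are fixed before allocation and already planned for collection, and the plan gives their adjusted analysis only hypothesis-generating standing. Adjustment would add about 0 to 1.5 points of power if the factors are weak to moderate and about 3 to 4 if they are strong. It would also protect the primary estimate against a hazard-ratio shift of about 3% to 9% at the 1.96-SD limit of imbalance in one factor. These sizes rest on assumed prognostic strengths and prevalences. The validity of the unadjusted analysis and its planned power are not in question.

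**What to change.** - Prespecify the primary complementary log-log model as treatment + Gustilo-Anderson class (I, II, IIIA) + OTA contamination (minimal, moderate, severe). Report the treatment-only model as the sensitivity analysis.
- Use the values recorded at the index operation, and say so. Participant timeline {13} allows baseline data to be collected up to 48 hours after the intervention, so the wording should tie both covariates to findings made before randomisation.
- Leave definitive fixation out of the primary model. The section on concomitant care {11d} allows index fixation to be temporary, so the definitive method may be settled after randomisation.
- Exempt this prespecified adjusted model from the hypothesis-generating wording in the additional-analyses section {20b}.
- State that the reported hazard ratio is conditional on the two factors.

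The cost is analysis wording only, with no change to sample size or data collection, and it should be settled while the statisticians are still masked. The one downside is that the conditional hazard ratio differs slightly from the marginal one, which the unadjusted sensitivity analysis will still show.

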### Objectives {7}

The primary objective of this study is to determine the efficacy of intraoperative, locally administered gentamicin versus placebo in the management of open tibial shaft fractures as measured by the prevention of fracture-related infection (FRI). Secondary objectives include assessing the efficacy of local gentamicin versus placebo on the occurrence of nonunion and unplanned fracture-related reoperations.

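### Fisher's exact test is offered as a method check on the primary FRI analysis but is specified on reoperation, so it changes the outcome as well as the method

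*Protocol article*

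**What the plan says.** The Primary outcomes section is unambiguous: "The primary outcome of this study will be the occurrence of fracture-related infection (FRI), a binary outcome". The primary analysis follows it: "The primary analysis will surround the occurrence of FRI as a binary outcome", fitted by binomial regression with a complementary log-log link so that available person-time is used.

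Reoperation sits elsewhere. Objectives {7} states: "Secondary objectives include assessing the efficacy of local gentamicin versus placebo on the occurrence of nonunion and unplanned fracture-related reoperations". The Secondary outcomes section defines it as a binary variable covering unplanned surgery for infection, wound healing or fracture union.

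The section on secondary and additional outcomes states this purpose for its analyses: "provide additional insight and support for the primary analysis and to assess whether the methodological choices we made had an undue effect on the results". It then promises Fisher's exact test on the 2 × 2 "cross-tabulation of the reoperation binary outcome and the treatment assignment" and comments: "This does not consider the observation time and thus is an independent statistical procedure and may yield different decisions than the primary prespecified analysis". The same section adds a risk difference with a 95% confidence interval from an identity-link binomial regression. That is contrasted with the main analysis, but no outcome is named for it.

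**The concern.** A method check is informative only if one thing changes at a time. To learn whether the complementary log-log model with person-time drives the conclusion, the same FRI outcome has to be analysed in another way. The plan instead attaches the alternative method to a different outcome and explains a possible discrepancy by the method alone.

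That affects how the results would be read. If the primary analysis and Fisher's test disagreed, a reader following the protocol would attribute the difference to observation time, when it could equally come from comparing infection with reoperation. If they agreed, the reader might take the FRI result as robust to method, when no second method had been applied to FRI. Settling the outcome after unmasking would also look data-driven, because the FRI and reoperation tables need not give the same answer.

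**Working it through.** The point rests on comparing sections. No computed figure establishes it.

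**1. Outcome and method of each analysis**

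| Analysis | Outcome named | Uses observation time | Stated role |
|---|---|---|---|
| Complementary log-log regression | FRI | Yes | Primary, two-sided alpha 0.05 |
| Fisher's exact test | Reoperation | No | Support for the primary analysis |
| Identity-link risk difference | None named | Not stated | Interval only, no P-value |

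Between the first two rows both the outcome and the method change. The text acknowledges only the method.

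**2. Are the two outcomes interchangeable?** Compare the definitions.

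- *FRI without reoperation.* Any one of four criteria suffices. A fistula, sinus or wound breakdown, or purulent drainage from the wound, can be found at a clinic visit. These cases count as FRI and need not count as reoperation.
- *Reoperation without FRI.* The definition includes surgery for delayed union or nonunion, such as bone grafting or implant exchange, and reoperation for hardware failure due to bone-healing problems. Neither requires infection. Surgery for wound-healing problems is also included and need not be FRI, although wound breakdown is itself an FRI criterion, so this part overlaps.
- *Overlap.* Debridement, soft-tissue coverage and amputation for infection would normally be events under both definitions.

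The outcomes are related but not the same, and each can occur without the other.

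**3. Which outcome does the reasoning need?** The section explains a possible difference from the primary decision solely by the neglect of observation time. With FRI in both analyses, that explanation is complete. With reoperation in one of them, the most obvious reason for a different decision, a different outcome, is left out. The stated purpose of testing methodological choices points the same way.

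**4. Is the FRI check specified elsewhere?** The article names no Fisher test of FRI. The risk-difference regression is the only candidate. Its contrast with the main analysis suggests FRI, but it directly follows the reoperation sentence and names no outcome, so it fills the gap only possibly.

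**5. Effect on the design figures.** The plan's sample size reproduces. Take 12% versus 6%, two-sided alpha 0.05, power 80%, 1:1 allocation and a pooled-variance z test. The mean rate is 0.09, so

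n = [1.96 × √(2 × 0.09 × 0.91) + 0.842 × √(0.12 × 0.88 + 0.06 × 0.94)]² / 0.06² ≈ 356 per arm.

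356 / (1 − 0.20) = 445 per arm, 890 in total, as stated. Changing the outcome of a supporting test alters none of this. For context, exact enumeration gives a two-sided Fisher test on FRI about 77% power with 356 evaluable per arm at these rates, against 80% for the z test, so the corrected check would be informative. This assumes that 12% applies to FRI. Sample size {14} says prior trial data "was used to estimate the base rate of reoperation at 12" per cent, so the protocol itself labels that figure a reoperation rate.

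**The case against.** The strongest defence is the section heading, which covers secondary as well as additional outcomes. Reoperation is a prespecified binary secondary outcome, the article names no other test for it, and a Fisher test of it would be legitimate there. The remark that it "may yield different decisions than the primary prespecified analysis" would also remain true. This reading is possible but does not rescue the text, because the purpose sentence and the observation-time explanation work only if the outcome is unchanged.

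Other parts of the defence stand. Fisher's test has no stated alpha, decision rule or stopping role, and the section says these analyses will be clearly separated from the primary outcome in reporting. Infection-related reoperations overlap with FRI, so the test as written gives some indirect support.

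A reader might infer more than the document supports:

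- *That the primary result is compromised.* It is not. The primary analysis is specified on FRI.
- *That no unadjusted comparison of FRI would ever be produced.* The risk-difference regression plausibly provides one, and the full protocol and analysis plan are not shown.
- *That reoperation was once the primary endpoint.* The reoperation base rate in the sample size section, and a stray remark in the primary-analysis section about separate trials each with its own alpha, may suggest borrowed text. Nothing in the article establishes that history, and the point does not depend on it.
- *That the design's expected event counts measure the error.* They describe the assumed rates and say nothing about how far the two tables would differ.

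**Conclusion.** The specification is wrong as written for its stated purpose, and the matter is of moderate importance. Fisher's test on reoperation does not assess whether the FRI conclusion is robust to method, and any comparison with the primary result confounds outcome with method. How often the two tables would lead to different decisions cannot be quantified, because the article does not give the overlap between FRI and reoperation.

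The conclusion rests on reading the test as a check on the primary analysis, which the purpose sentence and the observation-time contrast both support. If the unseen analysis plan already specifies the test on FRI, the published article contradicts it and still needs correcting.

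**What to change.** Before unmasking:

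1. In the sentence specifying Fisher's exact test, replace reoperation with FRI as the binary outcome.
2. State that the identity-link risk difference and its 95% confidence interval are also for FRI.
3. If a Fisher test of reoperation is wanted, list it separately as an analysis of that secondary outcome, without the comparison to the primary analysis.

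The cost is one changed word, one clarifying phrase, an optional extra line and the matching lines of code. Sample size, data collection and the primary analysis do not change. Because trial conduct is unaffected, the protocol's own provisions for minor corrections and clarifications appear to allow it as a recorded administrative change.
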